#### Enhancement of self-regulation skills

4.2.2

This intervention incorporates activities to enhance preschoolers’ general and food-related self-regulation abilities. Research suggests the primary facets of self-regulation in this age group are inhibitory control, working memory, and emotion regulation (47, 63).

Inhibitory control is the ability to halt an ongoing action when it is considered erroneous (64). The “Happy Goat Says” activity is designed to improve children's inhibitory control in the context of food selection (65). In this game, children are introduced to three types of items: healthy food, unhealthy food, and toys. A teacher prompts specific actions with the phrase “Happy Goat says.” The children are instructed to perform the actions only when the phrase is given, practicing restraint and remaining still otherwise.

Working memory is the ability to retain and manipulate information over short periods (66). We employ an “n-back” game with pictorial stimuli (fruits or vegetables) (65). Children must determine whether the current picture matches the one shown one or two steps earlier. The difficulty adjusts based on performance, gradually increasing to challenge each child's working memory capacity.

Emotion regulation refers to managing one's initial emotional reaction (67). To enhance these skills, the intervention incorporates an emotion management segment to the health curriculum. Teachers guide children in identifying various emotions by drawing facial expressions on toy eggs and teach simple relaxation techniques to help children cope with strong emotions.

These activities, grounded in developmental science and pilot-tested in three classes, were refined based on the initial outcomes and teacher feedback to ensure they are engaging and suitable for preschoolers. The self-regulation activities are integrated into the intervention schedule over three semesters, with the first two dedicated to weekly intensive activities, and in the final semester, they are reinforced bi-weekly. Each session lasts 10–15 minutes. Teachers received training and detailed instructions to maintain fidelity to the activity protocol while allowing minor adaptations to fit classroom context.

#### Promoting health-related behavior at home

4.2.3

The WPHS intervention extends beyond the classroom via family-centric healthy behavioral challenges, actively engaging parents in fostering a health-promoting home environment. Participating families are tasked with four distinct health challenges: (1) consuming five different fruits and vegetables daily, (2) choosing healthy snacks (e.g., milk or fruit) over high-energy-density alternatives, (3) engaging in ≥2 hours of outdoor physical activity daily, and (4) achieving 10 hours of sleep per night.

Progress is monitored through record cards that families update to track their adherence to these challenges. Trained teachers will regularly review these cards and provide feedback to both children and parents to encourage continued participation. Achievements are celebrated in the classroom with a “Reward Board” displaying badges for each child's accomplishments. Students who accumulate the most badges by the end of each term receive a special reward, further incentivizing healthy habits.

These family tasks are designed to maximize parental involvement and reinforce the health behaviors introduced in kindergarten. The challenges may be adjusted each term based on participation rates and feedback, allowing the intervention to remain responsive and effective.

### Family-level intervention

4.3

Parents and caregivers play a crucial role in shaping healthy diet and physical activity habits in children. The WPHS-intervention actively engages families to ensure the home environment supports healthy eating and physical activity. Family involvement includes:

#### Health education workshops

4.3.1

We will host two interactive workshops for parents (and grandparents) focusing on healthy parenting and lifestyle strategies to prevent childhood obesity. These sessions will provide practical guidance on nutrition, media use, physical activity, sleep, and strategies to foster self-regulation in children. Moreover, we have prepared a set of 37 concise health tips (delivered via handout or messaging) to reinforce essential concepts related to EBRBs and self-regulation, ensuring caregivers are well-informed and empowered to support healthy behaviors at home.

#### Customizing home environment guidance

4.3.2

We will provide personalized feedback to each family about their child's diet, activity, and sleep patterns, along with tailored recommendations to meet national guidelines. In addition, baseline information will be collected via the Food Frequency Questionnaire (FFQ) (68), a self-developed physical activity questionnaire, and the Children's Sleep Habits Questionnaire (CSHQ). Each family will receive a summary comparing their child's habits to the Chinese Dietary Guidelines and World Health Organization (WHO) recommendations for young children. Based on this, parents will be advised on specific adjustments (e.g, reducing sugary snacks, increasing physical activity, establishing consistent bedtimes) to optimize their home environment in support of their child's health.

### Enhancing the kindergarten environment

4.4

This component aims to improve the health knowledge of kindergarten staff, optimize the nutritional quality of school meals, and foster a health-centric atmosphere within the kindergarten. Key elements include:

#### Teacher professional development

4.4.1

Two training sessions for teachers will increase their health literacy in the classroom and enable them to promote child health. These sessions cover topics such as nutrition, physical activity, and strategies to encourage self-regulation in the classroom. Experienced teachers from the pilot kindergartens, who helped develop the curriculum, will deliver demonstration lessons to their peers within the intervention groups. This peer-led model ensures standardized understanding of the curriculum content and teaching methodologies across educators.

#### Themed weeks

4.4.2

Each kindergarten will implement periodic themed weeks aligned with the curriculum (e.g., “Active Play Week” or “Healthy Eating Week”). During these weeks, special activities will encourage physical activity, nutritious eating, and reduced screen time. Colorful posters aligned with the week's theme will be displayed on school bulletin boards to reinforce the health messages and generate enthusiasm among children and staff.

#### Nutritional optimization of school meals

4.4.3

The intervention will include a review of the menus provided in the kindergartens. Researchers will analyze the nutrients in school meals and provide recommendations to improve their nutritional balance. The intervention aims to align meals with the Dietary Guidelines for Chinese Preschool-aged Children (2022) issued by the Chinese Nutrition Society (69).

### Intervention outcomes

4.5

Evaluation of the WPHS intervention will focus on a comprehensive set of primary and secondary outcomes. The primary outcome is BMI z-score. Secondary outcomes include: (1) dietary behaviors (e.g., weekly intake of high-energy-density foods and sugar-sweetened beverages, and daily servings of fruits and vegetables), (2) sleep-related outcomes (e.g., average nightly sleep duration and sleep quality), (3) physical activity levels (e.g., time in moderate-to-vigorous physical activity and sedentary time), and (4) general and food-related self-regulation indicators (e.g., performance on the day-night task, less-is-more task, Corsi block-tapping task, digit span task, and scores on the Childhood Executive Functioning Inventory (CHEXI), and Children's Behaviour Questionnaire (CBQ) (5) other anthropometric indicators, including waist circumference, hip circumference, and body fat percentage (70).

## Data collection

5

Table 2 provides an assessment of metrics, methodologies, and data collection schedules used in the study. Trained research personnel will follow standardized protocols and utilize validated tools to ensure data accuracy and consistency across all time points. Assessments were conducted at three key intervals: T1 (baseline) in the second semester of the junior year; T2 (post-intervention) in the second semester of the mid-year; and T3 (follow-up) in the second semester of the senior year.

**Table 2 T2:** Overview of measurement indicators, instruments, and time point of assessment.

Data collection	Indicators	Assessment instruments	Time points of assessment
Measurement in kindergartens	• Height and weight	• Kangwa WS-RT-2U	• T1,T2,T3
	• Waist and hip circumference	• Measuring tape	• T1,T2,T3
	• Body fat percentage	• Multifrequency bioelectric impedance body composition analyzer Inbody 230	• T1,T2,T3
	• Skinfold thickness^a^	• Harpenden Skinfold calipers	• T1,T2,T3
	• Self-regulation level	• Self-regulation related tests	• T1, T2, T3
Actigraph GT3X+	• Physical activity and sleep^a^	• Actigraph GT3X+	• T1, T3
Questionnaire	• Basic information		• T1
	• Dietary behavior	• CEBQ (46), FFQ (48)	• T1,T2,T3
	• Sleep quality in children	• CSHQ (50)	• T1,T2,T3
	• General self-regulation level	• CBQ (51)	• T1,T2,T3
	• Food-related self-regulation level	• CEBQ (46)	• T1,T2,T3
	• Psychological behavior of children	• CBQ (51)	• T1,T2,T3

T1, the second semester of the junior year; T2, the second semester of the middle year; T3, the second semester of the senior year; CEBQ, Children's Eating Behavior Questionnaire; FFQ, food frequency questionnaire; CSHQ, Children's Sleep Habit Questionnaire; CBQ, Children's Behavior Questionnaire.

^a^
These indicators will be measured for some children but not all.

### Anthropometric measurement

5.1

Weight and height will be measured using calibrated scales and stadiometers [e.g., Kangwa (WS-RT-2U), accurate to 0.01 kg for weight and 0.1 cm for height]. To ensure reliability, each measurement will be taken twice. If discrepancies greater than 0.5 cm in height or 0.1 kg in weight are observed, a third measurement will be taken until the differences between any two consecutive readings fall below these thresholds. The average of the valid measurements will be used for subsequent analysis. Body composition will be estimated through Bioelectrical Impedance Analysis (InBody 230 device), which provides resistance readings used to calculate body fat percentage, fat-free mass, and fat mass.

Table 3 outlines the four tests of self-regulation used in the study, and their scoring. All fieldworkers will undergo comprehensive training to ensure standardized procedures across data collection.

**Table 3 T3:** The name and description of self-regulation-related tests.

Self-regulation	Name	Description
Inhibitory control	• Stroop test-Day and night (52)	Instruct children to respond in the opposite manner when answering questions, and present a series of cards with the sun or moon. In the presentation of a sun card, instruct children to respond with “night”, and when a card with stars and the moon is displayed, prompt children to answer “day”.
	• Less is more (53)	For food-related tasks, researchers will display various food toys and ask children to choose their preferred item for the experiment. The child will be prompted to indicate a bowl of food toys (containing 2 or 5 items), and the researcher will collect the chosen toys. Conversely, the child will receive the food toys they did not point to during the selection process.
	• Modified Stroop Task	In each trial, children were presented with various numbers of cherries and watermelons at the same time, and they were asked to indicate which set had more than the other, irrespective of fruit size. There were 64 trials per task variant, of which 50% congruent trials (where the larger number was represented by larger-sized stimuli, e.g., two cherries vs. five watermelons) and 50% incongruent trials (e.g., five cherries vs. two watermelons). The congruent trials and incongruent trials were randomly intermixed.
Working memory	• Corsi Block tapping task (54)	The researchers tap the blocks in a specific order, and the children are instructed to tap them in the same order and in reverse order. The difficulty of the test is progressively increased by sequentially adding more tapping blocks.
	• Digit span test (55)	This test involves a number table ranging from 2 digits to 13 digits. The researchers read a list of numbers, and the children are required to recite them both in order and in reverse order.
Executive function	• Childhood Executive Function Inventory	It consists of 24-items and comprises four scales: Inhibit, Shift, Working Memory, and Plan/Organize. Participants rate items on a five-point scale (i.e., Definitely not true, Not true, Partially true, True, Definitely true), with higher scores indicating lower executive function.

### Physical activity and sleep measurement

5.2

A subset of participants will be randomly selected to wear the Actigraph GT3X + accelerometer on the non-dominant wrist for seven consecutive days to objectively measure physical activity and sleep patterns. If any child fails to wear the device for 7 days, or if device issues arise, an additional week of monitoring will be scheduled for that child. The accelerometer data will be used to derive measures such as average daily activity counts, time spent in moderate-to-vigorous activity, sedentary time, and sleep duration (using validated cut-points and algorithms).

### Questionnaires

5.3

A structured questionnaire will capture demographic details and assess behaviors not captured by devices. This includes dietary intake [*via* the FFQ (71), CEBQ (72), sleep habits *via* the CSHQ (73), CHEXI (74), and the CBQ (75)]. These instruments are established measures with appropriate validity for our population.

## Quality control

6

A rigorous process evaluation will be conducted throughout the intervention to ensure it is delivered with high fidelity and reaches the target population effectively. We focus on three key elements: Recruitment/Reach, Dose Delivered (Completeness), and Fidelity.

For Recruitment/Reach, we will document recruitment and participation rates by tracking the number and characteristics of kindergartens and families that consent, alongside those who withdraw or are lost to follow-up. This will help identify any biases in reach and ensure the intervention is engaging the intended demographic. For Dose Delivered (Completeness), we will record the frequency and duration of all intervention activities (e.g., number of curriculum sessions taught, number of family challenge cards distributed and completed). We will also track the extent to which each component is implemented (for instance, tallying how many of the 32 curriculum sessions were delivered in each class, and how many health tips and posters were distributed as planned). Specifically, we will document the distribution of intervention materials, including 4 family task cards, 37 health tips, and 11 posters, to confirm they were provided to parents/caregivers and displayed in kindergartens as intended. For fidelity, we will verify that the intervention is executed according to the protocol. This includes tracking that children's behavioral challenge records are maintained, that classroom activities follow the lesson plan, and family engagement components occur on schedule. Trained evaluators will use checklists during random, unannounced visits to observe a sample of intervention sessions and ensure adherence to content and methods.

The process evaluation employs brief questionnaires with Likert-scale and open-ended items for teachers and parents to provide feedback on each component. This approach is designed to be time-efficient and not overly burdensome, while still providing comprehensive and quantifiable data. Table 4 presents a detailed overview of these process evaluation tools.

**Table 4 T4:** The process evaluation tools used in the WPHS-intervention.

Process evaluation tools	Process evaluation elements	Information/data collection
Recruitment log	Recruitment procedures	• Weekly monitoring of recruited kindergartens. • Tracking the number of kindergartens and children approached, those participated in baseline, entered the WPHS-intervention, and in the follow-up evaluation. • Documenting characteristics of kindergartens/children dropping out.
Teacher's Lesson Assessment Questionnaire	Dose delivered (completeness)	• Recording date, duration, quantity, and type of classroom sessions.
	Fidelity	• Noting any deviations or modifications made to original lesson plan. • Recording the start and end times of schedule activities. • Observing any unexpected changes or factors influencing adherence to the plan.
	Dose received (exposure and satisfaction)	• Teachers’ feedback on the comprehensibility, readability, relevance, credibility, attractiveness of the teaching materials. • Teachers’ feedback on children's behavior change with the WPHS project as implemented in the classroom. • Midpoint feedback from teachers regarding suggestions for improving the WPHS program and materials. • Teachers’ feedback on the barriers and facilitators for implementing each part of the intervention.
Attendance log	Dose received (exposure)	• Daily records of children's attendance in the kindergarten. • Identification of days when the WPHS-intervention activities are conducted. • Recording any factors affecting attendance.
Teachers’ post-intervention questionnaire	Dose received (exposure and satisfaction)	• Teachers’ reflections on the barriers and facilitators during the implementation of the WPHS project. • Feedback on the feasibility, attractiveness of the WPHS project. • Subjective feedback regarding observed behavioral changes in children's. • Subjective feedback on parents’, teachers’ and personnel's satisfaction with the WPHS project.
Teachers’ mid-intervention questionnaire	Dose received (exposure and satisfaction)	• Teachers’ reflections on the barriers and facilitators during the implementation of the WPHS project. • Feedback on the feasibility, attractiveness of the WPHS project. • Subjective feedback regarding observed behavioral changes in children. • Subjective feedback on parents’, teachers’ and personnel's satisfaction with the WPHS project.
Parent's post-intervention questionnaire	Dose received (exposure and satisfaction)	• Parents’ confirmation of receiving and/or reading each part of the material (tips, posters, family task cards). • Parents’ satisfaction with the WPHS project. • Parents feedback regarding the implementation of activities included in the material (family task cards) with their children at home. • Subjective feedback on observed behavioral changes in their child with the WPHS project. • Feedback was collected on the comprehensibility, readability, relevance, credibility, and attractiveness of the material (tips, posters, family task cards).
Parent's mid-intervention questionnaire	Dose received (exposure and satisfaction)	• Parents’ confirmation of receiving and/or reading each part of the material (tips, posters, family task cards). • Parents’ satisfaction with the WPHS project. • Parents feedback regarding the implementation of activities included in the material (family task cards) with their children at home. • Subjective feedback on observed behavioral changes in their child with the WPHS project. • Feedback on the comprehensibility, readability, relevance, credibility, and attractiveness of the material (tips, posters, family task cards).
Audit questionnaire	Physical and social environment, and the context of WHSP intervention	• Information on school food and physical activity environment (i.e., infrastructure/facilities/equipment, curriculum and personnel/health-related programmes in progress, which were related to the healthy lifestyle behaviours).
Researchers’ evaluation form	Dose delivered (completeness)	• We recorded the number and duration of training sessions
	Fidelity	• Venue of training. • Researchers who performed each training. • Records of the content of teacher training.
	Dose received (exposure and satisfaction)	• Numbers of teachers invited and attended. • Subjective assessment of teachers’ satisfaction with each training by the researchers who implemented the training.

## Statistical analysis plan

7

The statistical analyses will adhere to the intention-to-treat principle. Participants’ characteristics will be described by study arm. Continuous variables will be presented as mean (standard deviation) or median (interquartile range), depending on distribution, and compared between groups using Student's t-tests for normally distributed data or the Wilcoxon rank-sum test for non-normal variables. Categorical variables will be reported as frequency (%) and compared using the Chi-square test. To address missing data, multiple imputation by chained equations will be used to impute covariates.

The primary analysis will evaluate the impact of the intervention on the primary outcome (e.g., changes in BMI z-score) using a linear mixed-effects regression model. Because BMI z-scores are measured repeatedly for each child at multiple time points (T1-T3), the data have a hierarchical structure, with repeated measures nested within children and children nested within kindergartens. Linear mixed-effects models are therefore employed to account for within-subject correlations over time and clustering by kindergarten, by including random intercepts for both children and kindergartens. For dichotomous outcomes, logistic mixed-effects models will be employed. These models will incorporate a study group (intervention vs. control), and relevant covariates (kindergarten level, child age and sex, and maternal sociodemographic characteristics). The models will also account for the clustered design, and random intercepts for kindergarten and children will be included. Furthermore, the potential mediating role of self-regulation on the association between the intervention and weight status will be explored.

Stratified analysis will examine whether the intervention effect varies across different subgroups. Potential effect modifiers include kindergarten level, child gender, and child age.

All hypothesis tests will use a two-sided *α* = 0.05.

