### Sample size determination

3.2

The unit is randomization is the kindergarten. We calculated the sample size in Power Analysis and Sample Size (PASS) using a test for two means in a cluster-randomized design. Assuming each kindergartens contribute approximately 45 children, we determined that 11 kindergartens per arm (intervention and control) would provide 90% power (1-*β*) to detect an underlying difference of 0.28 (60) in the mean outcome (a medium standardized effect size) following the intervention. This calculation assumes an intra-class correlation coefficient (ICC) of 0.01 (61) at the two-sided significance level (*α*) of 5%. Assuming up to 20% attrition, we increased the sample to 26 kindergartens (13 intervention) (45 children/kindergarten), yielding an anticipated sample of 585 preschoolers receiving intervention.

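### The stated mixed model has no kindergarten-level variance for change in BMI z-score, so a group-by-time test would exceed 5% type I error whenever kindergartens differ in mean change

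*Protocol article*

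**What the plan says.** The Abstract gives change in BMI z-score as the primary outcome. Section 4.5 names BMI z-score without the word change. Section 7 (Statistical analysis plan) returns to change: the analysis addresses the "primary outcome (e.g., changes in BMI z-score) using a linear mixed-effects regression model".

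Section 7 then describes z-scores at T1, T2 and T3 as repeated measures within children, and children within kindergartens. It says that within-child correlation and kindergarten clustering are dealt with "by including random intercepts for both children and kindergartens", and states the same random effects again later in the paragraph. The fixed effects it names are study group and covariates. It names no time term, no group-by-time term and no kindergarten-by-time random effect. "All hypothesis tests will use a two-sided" 5% level.

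Section 3.2 makes the kindergarten the randomised unit and gives one ICC: "This calculation assumes an intra-class correlation coefficient (ICC) of 0.01". It gives no ICC of change.

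**The concern.** In a cluster trial, the standard error of the treatment effect must include the variance between clusters of the quantity being compared. Here that quantity is change from T1. A kindergarten intercept that is constant over time absorbs stable differences in level between kindergartens, but it drops out of any difference between visits. Differences between kindergartens in how much their children change then have no term of their own in the model, and children's changes are treated as independent within a kindergarten.

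Such differences are plausible. Section 3.3 enrols one class per kindergarten, so any class or teacher effect is a kindergarten effect, and meals and activity schedules are set at kindergarten level. If the differences exist, the confidence interval for the primary effect is too narrow and the nominal 5% test rejects too often.

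**Working it through.** **Inputs.** From section 3.2: 13 kindergartens per arm, 45 children each, 20% attrition (45 × 0.8 = 36 completers), ICC 0.01, difference 0.28. From section 7: two-sided 5%, rows T1 to T3, random intercepts for child and kindergarten. Assumed, because the documents give no figure: the ICC of change, the within-child correlation, and an SD of 1 (0.28 is called standardized).

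**The plan's own figure.** Two means at 90% power need 2 × (1.960 + 1.282)² / 0.28² = 268.1, so 269 per arm. The design effect at 45 per kindergarten is 1 + 44 × 0.01 = 1.44, giving 269 × 1.44 / 45 = 8.6, or 9 kindergartens per arm by the normal approximation. The stated 11 per arm gives 89.7% power with 36 completers and a t-test on 20 df, which matches 90%; with 45 it gives 93.7%. The point below does not depend on this.

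**Why the intercepts cancel.** Write the stated model as y = fixed effects + u(kindergarten) + c(child) + e(visit). For one child, T3 − T1 = change in fixed effects + e3 − e1; u and c are gone. With m children in each of 13 kindergartens per arm, the model variance of the between-arm contrast in T3 − T1 is 2 × 2s² / (13m), where s² is the within-child residual variance.

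Now suppose there is a kindergarten-by-visit component with variance τ², and let σ² be the child-level residual variance. The true variance is 2 × 2(σ² + mτ²) / (13m), while s² estimates approximately σ² + τ². With ρ = τ² / (τ² + σ²), the ICC of change:

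- true variance / model variance = 1 + (m − 1)ρ
- actual type I error = 2 × [1 − Φ(1.96 / √(1 + (m − 1)ρ))]

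| ICC of change | Ratio, m = 36 | Type I error | Ratio, m = 45 | Type I error |
|---|---|---|---|---|
| 0 | 1.00 | 5.0% | 1.00 | 5.0% |
| 0.005 | 1.175 | 7.1% | 1.22 | 7.6% |
| 0.01 | 1.35 | 9.2% | 1.44 | 10.2% |
| 0.02 | 1.70 | 13.3% | 1.88 | 15.3% |

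**How an ICC of change arises.** Hold the cross-sectional ICC at 0.01 and assume a within-child correlation of 0.8. If 20% of the kindergarten variance is specific to the visit, τ² = 0.002, σ² = 0.198 and ρ = 0.002 / 0.200 = 0.01. If 10% is visit-specific, ρ = 0.005; if none is, ρ = 0.

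**Simulation check.** Null trials with 26 kindergartens and three visits, 4,000 per setting, gave rejection rates for T3 − T1 under the random-intercepts model of 5.1%, 7.6% and 9.9% (m = 45) and 5.3%, 7.2% and 8.6% (m = 36) for 0%, 10% and 20% visit-specific variance. A t-test on kindergarten mean changes held 4.4% to 5.3% in every setting run. The closed-form standard error agreed with a fitted mixed model (0.0772 in both).

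**If the group main effect is tested instead.** The kindergarten intercept does not cancel; a cluster-level test of the overall means gave 4.5% to 5.2%. But the estimate averages over all three visits. For an effect δ at both T2 and T3 and none at T1, it targets (0 + δ + δ) / 3 = 2δ/3 in balanced data.

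**The case against.** The strongest objection is that the protocol never writes the group-by-time contrast. Section 7 names only study group and covariates, so the cancelling contrast is inferred from the primary outcome. This stands, and the point is therefore conditional. The other readings do not rescue the plan. The main-effect reading does not estimate change. If change scores were the outcome, a kindergarten intercept would model clustering of change directly, but section 7 describes z-scores at T1 to T3 as the repeated data, which does not fit.

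Three stronger conclusions are tempting, and the documents do not support them.

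- A reader might infer that type I error necessarily exceeds 5%. It does so only if kindergartens differ in mean change, and no document gives that variance. The Discussion expects uneven teaching and delivery between classrooms, but uneven delivery of an intervention with no effect does not by itself create differences under the null.
- A reader might infer an error rate of 20% or more. At an ICC of change of 0.05 the formula gives 23.7% (m = 36) to 27.3% (m = 45), but that is five times the only ICC in the plan.
- A reader might infer that the analysis discards the design effect of 1.44 used for sizing. Section 3.2 sizes the trial on a difference "in the mean outcome (a medium standardized effect size) following the intervention", a comparison of means and not of changes. The 1.44 is therefore not the plan's design effect for change, and the ratio of 1.44 in the table arises only because 0.01 is carried over as an assumption.

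**Conclusion.** The concern holds in conditional form. As written, the model either tests change with no kindergarten-level variance in its standard error, or tests a group main effect that is not change. In the first case type I error runs from 5% with no clustering of change to about 13-15% at an ICC of change of 0.02, and is about 9-10% if the plan's 0.01 carries over. In the second case type I error is about right, but an equal effect at T2 and T3 is diluted to about two-thirds. The algebra is firm; the size rests on an assumed ICC of change, balanced data and 36 to 45 children per kindergarten. This is not detail left to a fuller document: the article states the random-effects structure twice and says that it accounts for the clustering.

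**What to change.** State the primary contrast as group-by-time in the T1 to T3 model, say which visit or visits it concerns, and add a kindergarten-by-visit random effect to the child and kindergarten intercepts.

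A valid alternative is to analyse follow-up BMI z-score with T1 BMI z-score as a covariate and a kindergarten random intercept. It is not equivalent: the estimator, the handling of baseline and the precision differ, so one should be chosen in advance.

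In either case use small-sample degrees of freedom for 26 clusters (Kenward-Roger or Satterthwaite). A cut-off of 1.96 applied to a t statistic on 24 df has a true level of 6.2%. That detail can sit in the full analysis plan.

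The change is to analysis wording only. Intervals will be somewhat wider, and the added variance component may be estimated at zero, so the plan should say in advance what is done then.
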